**Fig. 1 fig0001:**
[figure not shown]
Experimental setup overview for the upper-limb XR biofeedback protocol. Participant wearing the Meta Quest 3 headset, wireless EMG sensors, and reflective markers while holding adjustable dumbbells within the Qualisys motion-capture volume with real-time motion tracking in Qualisys Track Manager (QTM).

### System architecture and integration

The experimental system comprises four hardware subsystems and two software services operating as a single integrated pipeline. Fig. 2 illustrates the complete architecture; each component is described below.

**Fig. 2 fig0002:**
[figure not shown]
System architecture and integration.

**Participant.** The participant wears six Delsys Trigno Avanti wireless EMG sensors on the bilateral deltoid muscles (detailed in Fig. 3) and reflective markers on anatomical landmarks (detailed in Table 2). Exercises are performed using adjustable dumbbells or resistance bands, depending on the protocol phase.

**Fig. 3 fig0003:**
[figure not shown]
Deltoid EMG sensor placement regions illustrated on the right shoulder. The same placement procedure will be mirrored on the left shoulder.

**Delsys Trigno System.** Six Avanti sensors transmit EMG signals wirelessly to the Trigno Research+ Base Station over a proprietary 2.4 GHz link. The base station sends the EMG channels to the workstation via USB, where they are ingested by QTM Software as analog input channels. This routing eliminates the need for a separate Trigno SDK process and consolidates all data acquisition within QTM.

**Qualisys Motion Capture System.** The cameras capture reflective-marker trajectories at 300 Hz and stream three-dimensional kinematic data to QTM over Ethernet. To synchronize the motion-capture and EMG recordings, the Qualisys Camera Sync Unit is configured in QTM to generate hardware TTL synchronization signals. Event generation is enabled, and the TTL signal polarity is set to negative. In the present configuration, Camera Sync Unit Out 1 operates in frequency-multiplier mode with a multiplier of 1 and a 50% duty cycle, producing a 300 Hz synchronization output with a 3333 μs period and a 1667 μs pulse duration. The output is connected to the trigger input of the Delsys Trigno Research+ Base Station using a BNC cable. QTM capture start and stop are controlled through the software-trigger function, with a 20,000 μs delay from the trigger signal to capture start or stop, a 100 ms hold-off time, and a minimum interval of 1 s between start and stop events. The Delsys base station transmits the synchronized EMG channels to the workstation through a USB connection, allowing the EMG and motion-capture data to be recorded using a common hardware timing reference.

**Workstation.** A high-performance desktop hosts two software services:•*QTM* Software receives the EMG and motion-capture streams, synchronizes them, and exposes the combined real-time data stream to network clients through the QTM SDK.•*MVIC Server* is a lightweight local server process (Node.js/Express) that stores per-participant MVIC normalization values and exposes them via a REST API, which the Unity application retrieves over Wi-Fi at session start.

**Meta Quest 3 (HMD).** The headset runs the Unity application as a standalone Android build. The Unity app receives synchronized EMG and kinematic data from QTM, retrieves MVIC normalization values from the MVIC Server, computes %MVIC, and renders the current visualization mode according to the participant’s randomized visualization-order sequence: avatar muscle coloring, dynamic bar indicators, or live EMG waveform graphs. Feedback is displayed either in a fully immersive VR environment or overlaid on the physical environment in MR passthrough mode.

Workstation Setup

Before each participant session, the workstation software is started in the following order: QTM Software, MVIC Server, and the Unity application on the Meta Quest 3 headset.

In QTM, the laboratory project template is loaded, the camera calibration is verified, and the Delsys EMG channels are checked as analog input channels. A short test recording is performed before the session to confirm that EMG and motion-capture data share the same start reference.

The MVIC Server is launched on the workstation as a local Node.js/Express service, and the participant-specific MVIC values are checked before running the exercise trials. The Unity application is then launched on the Meta Quest 3 headset and connected to the QTM real-time stream and MVIC Server. Before data collection, the researcher verifies that the avatar motion updates from the motion-capture stream and that the EMG visualization responds to brief voluntary deltoid contractions.

### Experimental protocol and procedures

Each participant will complete a single laboratory visit lasting approximately 120 min. The session will proceed through six sequential phases summarized in Fig. 7.

#### Phase 1: introduction, consent, and pre-screening

Upon arrival at the laboratory, participants will be briefed on the study objectives, procedures, potential risks, and their rights as research participants. Written informed consent will be obtained prior to any study procedures. Eligibility will be confirmed via a pre-screening questionnaire covering age, medical history, prior VR/MR experience, and exercise capability. The Shoulder Pain and Disability Index (SPADI) [15] will be administered as a screening instrument to confirm the absence of clinically relevant shoulder pain or disability prior to participation.

#### Phase 2: instrumentation and preparation

Phase 2 includes EMG sensor placement, reflective marker attachment, and headset fitting. For participants assigned to the VR or MR groups, the Meta Quest 3 headset will be fitted and adjusted to ensure optical clarity, comfort, and secure positioning before calibration.

##### EMG electrode placement

Six Delsys Trigno Avanti sensors will be placed bilaterally on the anterior, middle, and posterior deltoid muscles of each participant, following Surface Electromyography for the Non-Invasive Assessment of Muscles (SENIAM) recommendations [16]. Fig. 3 illustrates the deltoid placement regions, and Table 1 summarizes the placement location, orientation, starting posture, electrode size, inter-electrode distance, and reference information for each deltoid head.

**Table 1 tbl0001:** EMG sensor placement locations.

lectrode Location (SENIAM)	Orientation	Starting Posture	Electrode Size	IED
**· Muscle:** Anterior Deltoid **· Origin:** Anterior border, superior surface, lateral 1/3 of clavicle **· Function:** Shoulder flexion & medial rotation				
One finger width distal and anterior to the acromion	In the direction of the line between the acromion and the thumb	Sitting with the arms hanging vertically and the palm pointing inwards	Max 10 mm	20 mm
**· Muscle:** Middle (Medius) Deltoid **· Origin:** Lateral margin and superior surface of the acromion **· Function:** Shoulder abduction				
From the acromion to the lateral epicondyle of the elbow — at the greatest bulge of the muscle	In the direction of the line between the acromion and the hand	Sitting with the position of the trunk stable in relation to the arm. Stabilize the scapula if the fixation muscles are weak.	Max 10 mm	20 mm
**· Muscle:** Posterior Deltoid **· Origin:** Inferior lip of posterior border of spine of scapula **· Function:** Shoulder extension & lateral rotation				
Center the electrodes in the area about two finger-breadths behind the angle of the acromion	In the direction of the line between the acromion and the little finger	Erect sitting with the arms hanging vertically and the palm of the hand pointing inwards	Max 10 mm	20 mm

Before placement, the skin will be prepared by shaving excess hair if present, lightly abrading the site with fine sandpaper, and wiping with 70% isopropyl alcohol. Each sensor will be secured using a Delsys adhesive interface and circumferential medical tape, with the LED/logo oriented proximally to standardize alignment across participants.

##### EMG signal-quality assurance and artifact handling

EMG signal quality will be checked before and during each recording session. After sensor placement, each channel will be inspected at rest and during brief voluntary deltoid contractions to confirm clear physiological response, low resting noise, and absence of saturation, flatline behavior, or unstable wireless transmission. If a channel is noisy or unstable, the skin will be re-prepared, and the sensor will be re-secured or repositioned before recording.

During exercise trials, the researcher will monitor for signal dropout, saturation, sudden high-amplitude artifacts, or sensor movement. Trials affected by clear technical failure may be repeated or excluded, and the reason will be documented in the session log. During offline processing, raw EMG, filtered EMG, RMS envelopes, and %MVIC traces will be reviewed. Segments with severe dropout, saturation, or non-physiological artifacts will be flagged, and affected trials or channels will be excluded from the corresponding analysis when reliable feature extraction is not possible.

##### Reflective marker placement

Retroreflective markers will be attached to anatomical landmarks on the arms, shoulders, torso, pelvis, and lower limbs using the Qualisys Sports Marker Set. The marker set was selected because it supports biomechanically defined segment tracking and real-time skeleton generation through the Qualisys Skeleton Solver. The generated skeleton will be used to drive the full-body avatar in the immersive feedback application. The “Movable” markers listed in Table 2 indicate segment-tracking markers placed on body segments, such as the sternum, thigh, shin, upper arm, or pelvis, to improve segment tracking during dynamic movement. Joint centers will be estimated using functional calibration and landmark-based regression according to the Qualisys processing workflow.

**Table 2 tbl0002:** Detailed marker placement.

	#	Display Name	Location	Movable
	1	HeadFront	Forehead, above the nose.	-
	2	HeadL, HeadR	Just above the ear center.	-
	3	LShoulderTop, RShoulderTop	On top of the shoulder (bony prominence).	-
	4	LElbowOut, RElbowOut	On the outside of the elbow (bony prominence).	-
	5	LElbowIn, RElbowIn	On the inside of the elbow (bony prominence).	-
	6	LWristIn, RWristIn	On the inside of the wrist (bony prominence on the thumb side).	-
	7	LWristOut, RWristOut	On the outside of the wrist (bony prominence on the pinky side).	-
	8	Chest	Upper part of the sternum.	On the sternum
	9	WaistLFront, WaistRFront	On the front of the pelvis (bony prominence).	-
	10	LThighFrontLow, RThighFrontLow	Above the kneecap.	On the thigh
	11	LKneeOut, RKneeOut	On the outside of the knee (bony prominence).	-
	12	LKneeIn, RKneeIn	On the inside of the knee (bony prominence).	-
	13	LShinFrontHigh, RShinFrontHigh	Front of the shin.	On the shin
	14	LAnkleOut, RAnkleOut	On the outside of the ankle.	-
	15	LForefoot5, RForefoot5	On the base of the fifth toe.	-
	16	LForefoot2, RForefoot2	On the base of the second toe.	-
	17	SpineThoracic2	On the 2nd prominence below the biggest prominence on the top of the spine.	-
	18	LArm, RArm	On the back of the upper arm.	On the upper arm
	19	LHand2, RHand2	On the back of the hand at the base of the index finger.	-
	20	SpineThoracic12	A few cm below the midpoint of the lower tip of the shoulder blades.	-
	21	WaistBack	On the midpoint between the two prominences on the back of the pelvis.	-
	22	WaistL, WaistR	On the sides of the pelvis (bony prominence).	On the pelvis
	23	LHeelBack, RHeelBack	Back of the heel.	-

#### Phase 3: baseline and calibration measurements

Phase 3 comprises three sequential activities: (1) MVIC testing to establish EMG normalization references, (2) exercise familiarization using instructional videos, and (3) baseline exercise trials without immersive feedback.

##### MVIC protocol

MVIC testing will be used to establish per-muscle normalization references for all subsequent %MVIC calculations [16,17]. Contractions will be performed bilaterally, with the dominant side tested first. Resistance bands will be used to provide external resistance, as shown in Fig. 4, and the same research assistant will deliver standardized verbal encouragement throughout each trial (“Push! Push! Keep going!”).

**Fig. 4 fig0004:**
[figure not shown]
MVIC using a resistance band (A: anterior, B: middle, C: posterior).

**Positioning by muscle:**

**Anterior deltoid:** The participant sits with feet flat and trunk supported against the chair back. The arm is positioned at 90° shoulder flexion with the elbow extended and forearm neutral. The resistance band is secured at the hand/wrist and anchored to resist further shoulder flexion, and the participant pushes maximally upward.

**Middle deltoid:** The participant sits with the trunk stable. The arm is positioned at 90° abduction in the coronal plane with the elbow extended. The resistance band is secured at the hand/wrist and anchored to resist further abduction, and the participant pushes maximally outward.

**Posterior deltoid:** The participant sits with the trunk inclined forward. The arm is positioned at approximately 90° shoulder abduction/horizontal abduction with the elbow extended. The resistance band is secured at the hand/wrist and anchored to resist further horizontal abduction, and the participant pushes maximally backward.

Each muscle will be tested for 3 trials per side, resulting in 18 MVIC trials per participant. Each trial will include a 5 s maximal contraction, with 60 s rest between trials. The testing order will be fixed as anterior deltoid, middle deltoid, and posterior deltoid. The peak RMS value from the central 5 s of the highest-amplitude trial will be retained as the MVIC reference for the corresponding muscle and side. Exercise EMG will be expressed as:

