### Equipment and instruments

The experimental setup will include an immersive display, motion-capture, EMG sensing, exercise, and computing components, as shown in Fig. 1.•**Immersive display:** The Meta Quest 3 headset (Meta Platforms, Inc., Menlo Park, CA, USA) will be used for both VR and MR conditions. It provides standalone operation, inside-out tracking, high-resolution display, and full-color passthrough for MR feedback.•**Motion capture:** Kinematic data will be captured using a Qualisys motion-capture system with 12 Arqus A5 and 2 Miqus video cameras arranged around an approximately 10.0 × 6.0 × 2.5 m capture volume. Cameras will be positioned approximately 2.9 m above the floor and angled inward/downward to maintain shoulder-marker visibility. Calibration will use an L-frame and T-wand, with a target residual error below 0.5 mm. Cameras will be synchronized at 300 Hz. Reflective markers will follow the Qualisys Sports Marker Set to compute joint angles, range of motion, velocity, and smoothness metrics.•**EMG:** EMG data will be collected using six Delsys Trigno Avanti wireless sensors (Delsys Inc., Natick, MA, USA; Model SP-W06) connected to a Trigno Research+ Base Station (Model SP-W02). EMG will be sampled at 1926 Hz using the 20–450 Hz bandwidth setting. EMG and motion-capture recordings will be synchronized using a hardware TTL synchronization signal generated by the Qualisys Camera Sync Unit.•**Exercise equipment:** Adjustable dumbbells (2–5 kg) and resistance bands of varying resistance levels will be used for exercise tasks and maximum voluntary isometric contraction (MVIC) calibration.•**Computing infrastructure:** Data acquisition, VR and MR application development, and real-time signal processing will run on a workstation with an Intel i9–11900K processor, NVIDIA RTX 3060 Ti 8 GB GPU, 32 GB DDR4 RAM, and Windows 11. All data will be stored on secure, password-protected systems within the HCM Laboratory.

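### The MVIC reference is called isometric at a fixed arm position, but the only stated restraint is an elastic band of unspecified resistance, so the angle at which it is taken is not controlled

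*Protocol article*

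**What the plan says.** Under Equipment and instruments, the article states that "resistance bands of varying resistance levels will be used for exercise tasks and maximum voluntary isometric contraction (MVIC) calibration". Under MVIC protocol, "Resistance bands will be used to provide external resistance".

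Positioning by muscle then fixes a posture for each deltoid head. For the anterior head, "The arm is positioned at 90° shoulder flexion with the elbow extended and forearm neutral", and "The resistance band is secured at the hand/wrist and anchored to resist further shoulder flexion, and the participant pushes maximally upward". The middle head is tested at 90° abduction: "The resistance band is secured at the hand/wrist and anchored to resist further abduction, and the participant pushes maximally outward". The posterior head is tested at approximately 90°: "The resistance band is secured at the hand/wrist and anchored to resist further horizontal abduction, and the participant pushes maximally backward".

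There are three 5 s trials per muscle and side with 60 s rest between trials. The peak RMS of the highest-amplitude trial is kept. Its use is broad: "MVIC testing will be used to establish per-muscle normalization references for all subsequent %MVIC calculations".

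**The concern.** An elastic band increases its resistance only by lengthening. When a participant pushes maximally against it, the arm moves until band tension balances the effort, so a contraction restrained in this way is not secured at the position from which it starts. The angle reached depends on the band, its pre-tension and the participant's strength. The article names several resistance levels but gives no rule linking level to participant, muscle or side, and no check that the arm stayed in place.

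The value so obtained has three uses:
- it is the denominator of normalized muscle activation, which is listed among the primary outcomes;
- it sets the 10% MVIC onset/offset threshold for activation duration (EMG signal processing);
- it scales the values sent to the live display (Stage C of the runtime pipeline).

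Variation in the reference that has nothing to do with the participant's activation therefore enters a primary outcome and the feedback that participants see. The study is a single visit, so the reference cannot be re-measured later.

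**Working it through.** **The plan's own figure.** 3 deltoid heads × 2 sides × 3 trials = 18 MVIC trials, as stated. The article gives no band stiffness, pre-tension or strength, so the rest is reasoning and labelled illustration.

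**Step 1: is the position secured?** For all three heads the text names a start position and one restraint, the anchored band. It mentions no rigid stop, manual block or angle criterion. The trial kept is the one with the highest amplitude, wherever the arm was. The analysed window is described as 5 s of a 5 s contraction, so it does not set aside the phase in which the band stretches. By contrast, the dumbbell load has a selection rule and is recorded (Exercise familiarization and baseline trials).

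**Step 2: could the drift be material?** Illustrative static balance for the anterior test; every input is an assumption. Hand at L = 0.6 m from the shoulder, anchor D = 0.9 m below the hand, band tension at 90° T0 = 20 to 40 N, constant maximal hand force F = 50 to 120 N, band stiffness s. With the arm θ above the start position:
- band length l = √[(L − L cos θ)² + (D + L sin θ)²]
- tension T = T0 + s(l − D)
- the arm settles where T(D cos θ + L sin θ)/l = F

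| s (N/m) | Drift θ above 90° flexion |
|---|---|
| 1000 | 1.0° to 9.8° |
| 400 | 2.4° to 27.5° |
| 200 | 4.9° to 37.5° for F = 50 to 80 N; at 120 N not stopped within the 90° modelled |
| 100 | 10.4° to 42.6° for F = 50 N; at 80 N or more not stopped |

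Over these inputs the drift is never zero, it depends on both band and strength, and it is small only with a stiff band. The model gives an angle, not an EMG amplitude.

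**Step 3: what a shifted reference does.** Let r be the recorded reference divided by its fixed-position value. Then displayed %MVIC = true %MVIC / r, and the 10% threshold acts at 10r% of the fixed-position value. The direction is unknown, so both sides are shown:
- r = 0.9: a true 40 reads 40/0.9 = 44.4; the threshold acts at 9%.
- r = 1.1: a true 40 reads 40/1.1 = 36.4; the threshold acts at 11%.
- Two modes at 40 and 30 in the same muscle and side: (40/r)/(30/r) = 1.333 for any r. The ratio is unaffected.

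**Step 4: cost to between-participant comparisons.** Assume the reference contributes an independent relative error with CV e = 0.125 (for example, r with mean 0.8 and SD 0.1: 0.1/0.8), and that true %MVIC has CV c. Then total CV² = c² + e² + c²e².
- c = 0.3: 0.0900 + 0.0156 + 0.0014 = 0.1070; 0.1070/0.0900 = 1.19.
- c = 0.4: 0.1600 + 0.0156 + 0.0025 = 0.1781; 0.1781/0.1600 = 1.11.

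The between-participant SD rises by √1.19 − 1 ≈ 9% and √1.11 − 1 ≈ 5.5%.

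**The case against.** Four points count against a strong version of this concern.

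1. **Condensed article, missing figure.** Band level and anchoring are bench details that a full protocol may hold, and the set-up is shown in Fig. 4, which is not available here. A very stiff or strongly pre-tensioned band would keep the drift small, and the text does not exclude one. This limits how large the problem can be said to be. It does not remove it, because the text requires no such band, and elastic restraint is the stated method.

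2. **From angle to EMG.** A reader might infer that the band reference falls short of the true maximum, so that %MVIC is systematically inflated and the threshold acts below 10%. The documents do not support this. The reference is an EMG amplitude, not a force, and nothing shows whether it falls, rises or stays the same when the arm settles away from 90°. This objection stands in full.

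3. **Loss of a common reference.** A reader might also infer that %MVIC comparisons fail altogether. They do not. One reference per muscle and side serves the whole session, so it cancels from ratios between visualization modes and to the participant's own baseline.

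4. **Bias between groups.** Allocation to VR, MR and control is randomized, so variation in the reference adds noise to that comparison. Nothing in the text suggests that band choice differs by group. The kinematic outcomes and completion time do not use the reference.

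Keeping the best of three trials guards against one weak effort, but not against an uncontrolled position.

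**Conclusion.** The point holds in a limited form. The stated apparatus does not secure the stated isometric position, and nothing in the trial-selection rule would catch a departure from it. The affected quantities are absolute %MVIC compared across participants, muscles or sides, point differences on that scale, activation duration through the 10% threshold, and the scale of the live feedback.

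The size cannot be derived from the documents. The variance factor of about 1.1 to 1.2 rests on an assumed 12.5% reference error and an assumed true CV of 0.3 to 0.4; the drift angles rest on assumed stiffness, tension and force. This is a moderate loss of precision and interpretability that is worth removing before data collection. It does not invalidate the mode comparisons and is not a source of bias between the randomized groups.

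**What to change.** In MVIC protocol and Positioning by muscle, replace the elastic restraint with a non-stretch strap (or a band taken to its stretch limit), anchored in the same way for all participants, muscles and sides.

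Markers are attached in Phase 2, before MVIC testing, so record the shoulder angle during each contraction. Accept a trial only if the angle stays within a pre-stated tolerance of the described position over the analysed window. A tolerance of ±5° to ±10° would be an example; the figure is an assumption and is for the team to set. If a trial fails, re-anchor and repeat it after the 60 s rest already specified.

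The cost is a strap, a line or two of procedure, and an occasional repeated 5 s contraction with its rest.
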